### 2.4. Primary Clinical Outcome and Neural and Pharmacogenetic Mediators of Outcome

Our primary clinical arousal outcome will be the highest score on the arousal-based items of the clinician PAERS. The PAERS will be administered to all youth at baseline, and to high-risk youth weekly for the next 4 weeks then once every two weeks until week 16. We will explore subgroups of arousal due to worsening symptom severities of mania, anxiety, depression, psychosis, suicidality, and anxiety using clinician-, self-, and parent-reported (e.g., TEASAP [91]) measures of emotional reactivity and lability, and reaction times during the Continuous Performance Task with Emotional and Neutral Distracters (CPT-END) as secondary predictors of dysfunctional emotional arousal [93]. Heart rate, respiratory rate, and galvanic skin response will be collected while the participants undergo an MR scan during rest and during presentation of emotionally arousing stimuli as ancillary objective measurements of physiological arousal to support our neural predictions. Based on prior studies [29,51], we hypothesize that high-risk youth who develop antidepressant-related hyperarousal will exhibit, at baseline, greater physiological responses to emotionally arousing stimuli compared to high-risk youth who do not develop antidepressant-related hyperarousal. We will compare arousal in the MED and No MED conditions at its highest point between 4 and 16 weeks, which we believe will result in the most meaningful comparison across groups that also accounts for the possibility that some youth may improve with intervention.

#### 2.4.1. Neural Mediators

Our main neural outcomes are defined by prior studies implicating amygdala and VLPFC activation. We will evaluate activation in these regions during the emotional-neutral contrast of the Continuous Performance Task with Emotional and Neutral Distracters (CPT-END) task, a task of sustained attention with emotional and neutral pictures which we have used in our prior work examining prefrontal-limbic connectivity [94,95]. To assess the complex prefrontal-limbic circuit mechanisms that subserve antidepressant-related arousal both intrinsically at rest and during emotional arousal, youth will complete a resting state scan followed by the CPT-END in the MR scanner. Connectivity during the CPT-END and at rest will also be assessed. MRI data will be acquired at baseline for high-risk youth and controls, and at 4 weeks in high-risk youth using a 3.0 Tesla GE whole-body MRI scanner located at Cincinnati Children’s Hospital Medical Center Imaging Research Center and Stanford’s Richard M. Lucas Center for Imaging. An additional MRI scan will be acquired in any high-risk youth who develops antidepressant-related dysfunctional emotional arousal prior to 4 weeks, or up to one additional scan after 4 weeks if a hyperarousal event occurs between 4–16 weeks.

Participants will complete two fMRI runs of the emotionally arousing CPT-END task, in which whole-brain images (volumes) will be acquired every 3 s using a T2*-weighted gradient-echo echo-planar imaging pulse sequence. We will explore whether high-risk youth who do not develop antidepressant-related arousal benefit from antidepressant treatment, which has been documented to reduce amygdalar activation [96]. For those high-risk youth who are not exposed to escitalopram, we predict that there will be effects on limbic activation and connectivity due to a combination of psychotherapeutic effects [97], trait vulnerability to prefrontal-limbic dysfunction [35], and a natural propensity toward symptom progression [98]. We hypothesize that early change (baseline to 4 weeks) in the level of amygdala hyperactivity will predict the level of subsequent arousal (highest after the 4-week scan) and that the correlation between changes in neural circuitry and the level of subsequent arousal is stronger in the MED condition compared to the No MED condition (Figure 2).

#### 2.4.2. Pharmacogenetic Mediators

Our main pharmacogenetic-related mediators are *CYP2C19* metabolizer phenotype and serum escitalopram level. At 8 weeks or discontinuation of study participation (if earlier), we will obtain a sample for pharmacogenetic testing with the GeneSight Psychotropic assay. *CYP2C19* metabolizer phenotypes will be determined using Clinical Pharmacogenetics Implementation Consortium (CPIC) guidelines [99] and classified as normal (NM), rapid (RM), ultrarapid (UM), intermediate (IM), or poor (PM) metabolizer phenotypes. We will also perform a blood draw at 8 weeks or at early termination to determine serum escitalopram levels via mass spectrometry. Serum escitalopram concentration, *CYP2C19* metabolizer phenotypes, and medication adherence data will be integrated and modelled using MWPharm++ to determine pharmacokinetic parameters such as the maximum serum concentration (C_max_), the 24 h area under the curve (AUC_24_), the elimination half-life (t_1/2_), and clearance (CL) of escitalopram. Genetic testing reports will identify alleles in other genes as well (e.g., *CYP2D6*, *CYP2C9*, *CYP1A2*, *SLC6A4*, and *HTR2A*) and we will explore associations between these alleles and outcomes such as treatment efficacy and rates of adverse events. Based on similar studies of escitalopram in youth [64,65], we predict that high-risk youth with reduced *CYP2C19* metabolizer phenotypes will have higher C_max_ and/or AUC_24_ and higher rates of arousal symptoms than high-risk youth with normal or elevated *CYP2C19* metabolizer phenotypes.

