## Abstract

Antidepressants are standardly used to treat moderate to severe symptoms of depression and/or anxiety in youth but may also be associated with rare but serious psychiatric adverse events such as irritability, agitation, aggression, or suicidal ideation. Adverse events are especially common in youth with a family history of bipolar disorder (BD) who are at heightened risk for dysfunction in neurobiological systems that regulate emotion and arousal. To further understand this phenomenon, this study will examine (a) baseline risk factors associated with dysfunctional arousal in a sample of youth at high-risk for BD treated with or without an antidepressant, (b) whether antidepressant-related changes in arousal are mediated by changes in prefrontal-limbic circuitry, and (c) whether pharmacogenetic factors influence antidepressant-related changes in arousal. High-risk youth (aged 12–17 years with moderate to severe depressive and/or anxiety symptoms and at least one first-degree relative with bipolar I disorder) will be randomized to receive psychotherapy plus escitalopram or psychotherapy plus placebo. Neuroimaging and behavioral measures of arousal will be collected prior to randomization and at 4 weeks. Samples for pharmacogenetic analysis (serum escitalopram concentration, *CYP2C19* metabolizer phenotype, and *HTR2A* and *SLC6A4* genotypes) will be collected at 8 weeks. Youth will be followed for up to 16 weeks to assess change in arousal measures.

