### 1.3. Escitalopram Pharmacogenetics in High-Risk Youth

Our study will use escitalopram, a selective serotonin reuptake inhibitor (SSRI), which is commonly used to treat depressive and anxiety disorders in children and adolescents [59]. Escitalopram is safe and effective for treating pediatric major depressive and generalized anxiety disorders [60], and is approved by the US Food and Drug Administration (USFDA) for the treatment of major depressive disorder in youth ages 12 and older. Additionally, escitalopram is well-tolerated and cost-effective [61,62]. Given the previously noted risks of developing any psychopathology [54] and/or experiencing a hyperarousal event in response to SSRIs [8,20] among youth at risk for BD, pharmacogenomic assays may provide targeted information about risks for adverse events in these youth (including hyperarousal) during treatment with escitalopram [63]. Modern genetic testing allows for quick genotyping for dozens of genetic polymorphisms which are identified as potential genes of interest in predicting treatment outcomes and rates of adverse events during treatment with escitalopram.

In this study, we will obtain a genetic sample from all high-risk youth to identify pharmacokinetic and pharmacodynamic risk alleles. Pharmacokinetic genes of interest include enzymes involved in the metabolism of escitalopram, including members of the cytochrome P450 (CYP) family, such as *CYP2C19*, *CYP2D6*, and *CYP1A2* [33,63,64]. CYP2C19 plays a significant role in the metabolism of escitalopram, and multiple single nucleotide polymorphisms (SNPs) in *CYP2C19* are linked to differences in the rate of escitalopram metabolism [65,66]. Multiple studies suggest that escitalopram dosing regimens should be modified based on *CYP2C19* alleles to achieve comparable therapeutic serum concentrations of escitalopram, as some genotypes confer a greater risk of therapeutic failure or adverse events [64,65,66,67]. Notably, individuals with BD, as compared to those with MDD, have poorer metabolism via CYP2C19, which may predispose them toward antidepressant-induced hyperarousal [68] (see Figure 1). Among adolescents with anxiety disorders treated with escitalopram who experienced hyperarousal, a greater maximum concentration (C_max_) and area under the curve (AUC) of blood serum concentrations of escitalopram was observed compared with adolescents who did not experience hyperarousal symptoms [64].

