### 2.6. Limitations

The proposed study will gather data on high-risk youth only during a 16-week period, so this study cannot determine whether there are long-term risks or delayed effects of antidepressant exposure in high-risk youth far beyond the duration of the study. We expect that most children who enroll in our study may still live with their first-degree relatives with BD, so our study cannot easily differentiate between the mental health risks posed by heritable genetic factors as opposed to the stress of living with a family member (especially a parent) with a serious psychiatric disorder. Treatment adherence will be well-tracked, but achieving reliable medication adherence in adolescents remains challenging. Even though minor lapses in medication adherence may have relatively little effect on clinical or neuroimaging outcomes, missed or extra doses may introduce significant noise into pharmacokinetic data. For example, serum escitalopram levels can vary greatly when doses are missed in the week before blood samples are drawn. Furthermore, youth who experience hyperarousal symptoms may be more distressed and consequently less likely to participate in some inherently stressful aspects of the study, such as entering the MR scanner or providing a cheek swab or blood sample for pharmacogenetic analysis. Finally, we expect that most youth enrolled in this study will be medication-naïve, but some study participants may be allowed to take concomitant psychostimulants or alpha-2 agonists before and during the study, and this may also confound results.

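### The pharmacogenetic DNA sample is taken at week 8 or exit although genotype is fixed, so it is liable to be missing more often in youth who become hyperaroused before or around week 8

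*Protocol article*

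**What the plan says.** All references are to the protocol article.

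- **Timing.** Section 2.4.2 states: "At 8 weeks or discontinuation of study participation (if earlier), we will obtain a sample for pharmacogenetic testing with the GeneSight Psychotropic assay". The Abstract gives the same week for the genotypes: "genotypes) will be collected at 8 weeks". No section describes a DNA sample at baseline, although high-risk youth already have the PAERS and an MRI scan then (sections 2.4 and 2.4.1).
- **Intended coverage.** Section 1.3 says "we will obtain a genetic sample from all high-risk youth to identify pharmacokinetic and pharmacodynamic risk alleles".
- **Acknowledged risk.** Section 2.6 notes that "youth who experience hyperarousal symptoms may be more distressed and consequently less likely to participate in some inherently stressful aspects of the study", and among the procedures concerned it names "providing a cheek swab or blood sample for pharmacogenetic analysis". It gives no rate and no remedy.
- **Hypothesis that uses the genotype.** Section 2.4.2 predicts that youth with reduced CYP2C19 metabolism will show "higher rates of arousal symptoms than high-risk youth with normal or elevated" CYP2C19 phenotypes.
- **Outcome window.** Section 2.4: "We will compare arousal in the MED and No MED conditions at its highest point between 4 and 16 weeks".

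**The concern.** The serum escitalopram level has to be measured on treatment. The genotype does not: it is the same before randomisation as at week 8. Taking both at the same late visit means that capture of a fixed trait can depend on what has happened to the participant since randomisation.

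Here the event that may reduce capture is hyperarousal, which is also the outcome in the CYP2C19 hypothesis. If the authors' own worry in section 2.6 proves right, the genotype–arousal analysis loses cases faster than non-cases. Cases carry most of the information in that analysis, and they will be few. The mixed-effects model in section 2.5 is chosen partly for its handling of missing data. That advantage concerns missing repeated outcomes; the model does not by itself recover a missing person-level predictor such as genotype.

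**Working it through.** **1. The plan's own figure.** The only power figure is in section 2.5: 0.82 for the MED versus No MED effect on change in amygdala hyperactivity, with 100 and 50 youth, d = 0.5 and two-sided alpha 0.05. The noncentrality is 0.5 × √(50 × 100/150) = 2.887. Power is 0.823 by the normal approximation and 0.818 by the t distribution with 148 degrees of freedom. The figure reproduces. It does not involve genotype, so this point leaves it unchanged.

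**2. Effect on risks by genotype.** The documents give no hyperarousal risk and no missingness rate, so all inputs in this step are assumptions. True risk p is 0.40 in reduced metabolisers and 0.20 in the others. Genotype is missing in a fraction m1 of cases (0.30 or 0.40) and m0 = 0.10 of non-cases.

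Observed risk = p(1 − m1) / [p(1 − m1) + (1 − p)(1 − m0)]

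| m1 | Reduced metabolisers | Others | Difference |
|---|---|---|---|
| none missing | 40.0% | 20.0% | 20.0 points |
| 0.30 | 0.28/(0.28 + 0.54) = 34.1% | 0.14/(0.14 + 0.72) = 16.3% | 17.9 points |
| 0.40 | 0.24/(0.24 + 0.54) = 30.8% | 0.12/(0.12 + 0.72) = 14.3% | 16.5 points |

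The share of cases lost is m1 itself, 30% or 40%.

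**3. Effect on the odds ratio.** The true value is (0.40/0.60)/(0.20/0.80) = 2.67. With m1 = 0.40 it is (0.24/0.54)/(0.12/0.72) = 2.67, and with m1 = 0.30 it is (0.28/0.54)/(0.14/0.72) = 2.67. The factor (1 − m1)/(1 − m0) cancels whenever missingness depends on the event alone.

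**4. Effect on precision, over a wider assumed range.** Take the 100 MED youth, with 20–30% reduced metabolisers, risks of 40–50% versus 20%, and genotype captured in 95% of non-hyperaroused and 50–80% of hyperaroused youth.

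- Full capture: 24–29 expected events genotyped, risk difference 0.20–0.30, power 0.47–0.85.
- Selective capture: 12–23 events genotyped, risk difference 0.14–0.28, power 0.34–0.79. Scenario by scenario, the risk difference shrinks by about 6–29% and power falls by about 5–20 points.
- For comparison, a non-selective 5% loss costs only about 2 points of power (for example 0.469 to 0.452).

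**5. Continuous score.** The primary arousal outcome is a PAERS score. Assume a true difference of 0.5 SD by phenotype, call the top 25% hyperaroused, and use the capture rates of step 4. The observed difference is 0.43–0.48 and power falls from 0.52–0.63 to 0.38–0.57.

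**6. Which events can act on the sample.** The outcome window runs from week 4 to week 16, and sampling is at week 8 or at exit if earlier. Hyperarousal that first appears after week 8 cannot cause refusal at week 8. Steps 2 to 5 apply the loss to all cases and therefore sit at the upper end.

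**The case against.** The case against giving this much weight has several parts.

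- **The protocol has a fallback.** Youth who leave before week 8 are to be sampled on leaving. This reduces the loss. It does not remove it, because it needs cooperation from the same distressed youth whom section 2.6 describes.
- **Stopping the drug is not leaving the study.** Section 2.3 links discontinuation of study medication to worsening activation and functioning. A reader might infer that these youth are lost to genotyping. The text does not say so, and visits every two weeks to week 16 would allow a later swab. No repeat attempt is promised, however.
- **Selective loss is a possibility, not a stated fact.** A reader might infer that genotype will go missing in the hyperaroused. Section 2.6 says only that they may be less likely to take part, and no rate is given. This stands.
- **The relative association survives.** A reader might infer that the estimated genotype effect is biased on every scale. Under the illustration the odds ratio is exactly preserved. This stands, on the condition that missingness depends on the event alone.
- **The randomised comparison is untouched.** Arousal by metaboliser phenotype is not a randomised contrast, so loss of genotype does not damage the MED versus No MED comparison. This stands.
- **The pharmacokinetic part gains little.** Peak concentration and area under the curve still need the week-8 or exit blood draw, which is exposed to the same refusal. This stands.
- **The authors disclose the limitation.** They do, but for the swab, unlike the blood draw, it can be avoided.

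**Conclusion.** The point holds as a cheap design improvement. A fixed trait is sampled at a time when its capture can depend on the outcome it is meant to predict, and the protocol itself names that dependence as possible. The intention to sample all high-risk youth is put at avoidable risk.

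The size cannot be determined from the documents. Under the assumed 40% and 20% risks, with 30–40% of cases and 10% of non-cases missing, the risk difference falls from 20 to about 16–18 points and 30–40% of cases are lost. The true effect is likely to be smaller, because only events before or around week 8 can drive refusal and because the exit sample recovers some youth.

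The harm is confined to the genotype–arousal analysis: fewer events, less precision, and attenuated absolute risks and mean differences. The documents do not support the stronger conclusions that selective loss is certain, that the odds ratio is biased, or that the treatment comparison or the 0.82 power is compromised.

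**What to change.** Take the cheek swab from every high-risk youth at the baseline visit, before randomisation. Either store it, or run it and hold the report from blinded staff until the time at which the current plan would release it, so that blinding and care are unchanged. Keep the week-8 or early-termination blood draw for serum escitalopram only. Align the Abstract and section 2.4.2 with the new timing, and limit the remark in section 2.6 to the blood sample and the scan.

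The cost is moving one existing procedure to an existing visit, handling the held reports, and a few extra assays for youth who leave early. The change removes hyperarousal as a cause of missing genotype. It does not recover pharmacokinetic parameters for youth who refuse the blood draw.

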### 2.2. Randomization

High-risk youth will be randomized to receive double-blinded treatment with psychotherapy plus escitalopram (MED) vs. psychotherapy plus placebo (No MED) in a 2:1 ratio using block randomization with a block size of six. Randomization will be stratified within sites with respect to diagnoses (anxiety only, depression only, or anxiety and depressive symptoms), family history load (i.e., ≥3 first- or second- degree relatives with bipolar disorder vs. 1–2 first- or second-degree relatives with bipolar disorder), and the presence (vs. absence) of concomitant stimulant or alpha-2 agonist treatment. 

We selected psychotherapy (No MED) as the most ethically reasonable comparator for youth presenting with clinically significant symptoms of depression or anxiety. All participants (No MED and MED) will be assigned a study-trained therapist who will provide hour-long, up to weekly, individual cognitive-behavioral therapy or family-focused therapy (FFT) for high-risk youth [87,88]. FFT is a semistructured treatment that is protocol-driven and incorporates psychoeducation about mood and stress vulnerability models for depression/anxiety, structured communication training among family members, and problem-solving skills. Sessions will be weekly for the first 4 weeks, then participants will be given the option to continue meeting weekly or once every two weeks for an additional 12 weeks.

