### 2.3. Medication Dosing and Accountability

High-risk youth in the MED condition will be treated with escitalopram and monitored by a child and adolescent psychiatrist who is blinded to treatment assignment. Each high-risk participant will be assessed weekly for the first 4 weeks, then once every two weeks until 16 weeks. Escitalopram will be initiated at 5 mg daily for 1 week, then titrated to 10 mg daily for 1 week, then titrated to a target dose of 20 mg daily (maximum dose 30 mg/day). Titration will proceed no faster than 5 mg/week. Clinicians will carefully monitor participants for treatment response based on symptom severity rating scales of anxiety (PARS), depression (CDRS-R), (hypo)mania (Young Mania Rating Scale) [89], and the emergence of dysfunctional emotional arousal using the clinician-version of the Pediatric Adverse Events Rating Scale (PAERS) [90] and the parent-rated Treatment-Emergent Activation and Suicidality Assessment Profile (TEASAP) [91]. Escitalopram (or placebo) will be discontinued if there is a 2-step worsening on the Clinical Global Impression-Severity of Activation (CGI-SA) scale [91] compared with baseline and a Children’s Global Assessment Scale (CGAS) [92] score of <55.

Adherence, based on pill count, will be obtained at each visit. First, participants will receive weekly clinical follow-ups during dose titration, then clinical follow-ups every two weeks until week 16 to closely monitor for treatment adherence. Blood samples for analysis of serum escitalopram and desmethylescitalopram concentrations will be drawn at 8 weeks or at early termination if sooner than week 8. We aim to recruit medication-naïve youth but recognize that some high-risk youth who are seeking treatment for significant symptoms may be exposed to prior psychotropic medications. We will consider the role of past medications in our analysis of primary outcomes, and participants will be allowed to continue stable doses of concomitant stimulants and alpha-2 agonists. 

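### The predicted difference in C_max and AUC24 between CYP2C19 phenotypes is partly built in, because phenotype is an input to the model that estimates those parameters

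*Protocol article*

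**What the plan says.** Section 2.4.2 of the protocol article names three inputs to the pharmacokinetic model: "Serum escitalopram concentration, *CYP2C19* metabolizer phenotypes, and medication adherence data will be integrated and modelled using MWPharm++ to determine pharmacokinetic parameters". The outputs are parameters "such as the maximum serum concentration (C_max_), the 24 h area under the curve (AUC_24_), the elimination half-life (t_1/2_), and clearance (CL) of escitalopram".

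The same section then states the hypothesis: "we predict that high-risk youth with reduced *CYP2C19* metabolizer phenotypes will have higher C_max_ and/or AUC_24_ and higher rates of arousal symptoms", the comparison being with youth of normal or elevated phenotype.

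The measured pharmacokinetic information is one scheduled sample per youth: "We will also perform a blood draw at 8 weeks or at early termination to determine serum escitalopram levels via mass spectrometry". Section 2.3 agrees: "concentrations will be drawn at 8 weeks or at early termination if sooner than week 8". Section 2.6 warns that "serum escitalopram levels can vary greatly when doses are missed in the week before blood samples are drawn".

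Section 2.4.2 also states: "Our main pharmacogenetic-related mediators are *CYP2C19* metabolizer phenotype and serum escitalopram level". The article does not say that the phenotype comparison will use parameters estimated without phenotype, or the measured level alone.

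**The concern.** The grouping variable of the hypothesis helps to generate its outcome. One concentration cannot by itself identify C_max, AUC24, half-life and clearance, so a model has to supply the rest. If phenotype informs the model, each youth's estimate is pulled toward a phenotype-specific value. Comparing the estimates by phenotype then returns part of the difference the model assumed, even where the measured levels do not differ. The noisier the single level, the larger that part, and section 2.6 accepts that it can be noisy.

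At stake is one pharmacogenetic prediction. A reported link between phenotype and exposure could reflect the software's assumption more than the trial's data, and its p-value would not have its nominal error rate.

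**Working it through.** **Plan's own figure.** The article gives no figure for this comparison. Its only design calculation (section 2.5) is power 0.82 for d = 0.5 with 100 MED and 50 No MED. This reproduces: 0.823 by normal approximation and 0.818 by the exact t distribution. It is used here only as the source of the 100 MED youth.

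**Inputs from the article.** 100 MED youth; one level per youth; phenotype in the model; modelled AUC24 compared by phenotype.

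**Assumptions, not in the article.**
- 30 reduced versus 70 other metabolizers, all with usable data
- between-subject log-SD w = 0.4
- residual log-SD of the single-sample estimate s = 0.2, 0.3 or 0.4
- AUC ratio R built into the model = 1.3, 1.5 or 2.0
- no true difference

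**Formula.** With y the log AUC implied by the sample alone, the individual estimate is a precision-weighted average:

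e = B·y + (1 − B)·(phenotype-specific prior mean), where B = w²/(w² + s²).

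B is 0.80, 0.64 and 0.50 for s = 0.2, 0.3 and 0.4. With no true difference:

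- spurious log ratio = (1 − B)·ln R
- SD of e within a group = B·√(w² + s²)
- standard error = that SD × √(1/30 + 1/70) = SD × 0.218

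**Middle case (R = 1.5, s = 0.3).** The shift is 0.36 × 0.405 = 0.146, a ratio of 1.16. The SD is 0.64 × 0.5 = 0.32, the standard error 0.070 and the shift over its standard error 2.09. A two-sided 5% t test with 98 degrees of freedom rejects 54% of the time.

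**Full grid, no true difference: spurious AUC ratio and rejection rate.**

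| s | R = 1.3 | R = 1.5 | R = 2.0 |
|---|---|---|---|
| 0.2 | 1.05, 10% | 1.08, 18% | 1.15, 42% |
| 0.3 | 1.10, 27% | 1.16, 54% | 1.28, 94% |
| 0.4 | 1.14, 56% | 1.22, 90% | 1.41, 100% |

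Simulation at 4,000 runs per setting agrees. With phenotype left out of the estimator, rejection is 4.5% to 5.4%.

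**Other assumptions.** A separate simulation used reduced-phenotype shares of 15% and 30%, model clearance ratios of 0.8, 0.7 and 0.5, and between-subject/residual SDs of 0.4/0.2, 0.4/0.4 and 0.3/0.5. It gave false-positive rates of 7% to 100% and spurious ratios of 1.05 to 1.67. Without phenotype the rates were 4.3% to 5.6% and the ratio 1.00.

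**If a true ratio T exists.** The phenotype-informed estimate centres on T^B × R^(1−B).
- T = 1.2, R = 1.5: 1.26, 1.30 and 1.34 for s = 0.2, 0.3 and 0.4.
- T = R = 1.5: 1.50, so no bias.

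The phenotype-blind shrunken estimate centres on T^B. For T = 1.5 that is 1.38, 1.30 and 1.22 to 1.23.

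**The case against.** The strongest reply has four parts.

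**The null is not the expected state.** Section 1.3 says CYP2C19 matters for escitalopram metabolism. If the model's assumed ratio is right, the phenotype-informed estimate is unbiased. This stands as far as it goes, and it means the false-positive rates describe a case the investigators think unlikely. It does not rescue the test: a comparison that gives the right answer only when its assumption is right is not evidence for that assumption.

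**The size is unknown.** The article gives neither the model structure nor the weight of phenotype in it, and may leave both to a fuller document. This stands for the size. The existence and direction of the bias follow from what the article does fix: phenotype goes in, and the outputs are compared by phenotype. A phenotype term with no effect would remove the bias, but then listing it as an input would serve no purpose.

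**The measured level also enters.** True, and for that reason the result is only partly predetermined.

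**The reach is narrow.** This stands in full. A reader might infer that the circularity compromises the whole pharmacogenetic aim or the mediation analysis. The documents do not support that. The named main mediators are an assayed phenotype and a serum level; the level is measured by mass spectrometry, and neither is stated to be a model output. The phenotype-versus-arousal prediction sets a genotype against arousal symptoms, with no modelled quantity. A reader might also infer that AUC24 will act as a proxy for genotype in an exposure-arousal analysis, but no section plans modelled AUC24 or C_max as a predictor of arousal in this trial. The choice left open between C_max and AUC24 is a separate multiplicity question, not examined here.

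**Conclusion.** The point holds for one comparison: modelled C_max or AUC24 between CYP2C19 phenotypes. Followed as written, the plan biases it toward the ratio that the model assumes; if no true difference exists, that is toward the predicted result.

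The size cannot be derived from the document. The spurious AUC ratio of 1.05 to 1.41 and false-positive rate of about 10% to 100% (54% in the middle case) rest wholly on the stated assumptions, apart from the 100 MED youth. Even complete data on all 100 is optimistic, since section 2.6 expects some distressed youth to be less willing to give samples. These rates belong to this one test and are not an error rate for the trial. The main mediators, the phenotype-versus-arousal prediction and the MED versus No MED comparison are unaffected.

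Severity: should-fix.

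**What to change.** State that the phenotype-versus-exposure comparison will not use phenotype-informed parameters. Use one of these instead:

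1. **Preferred:** the measured serum escitalopram concentration, normalised for dose and time since last dose and accounting for adherence, compared by phenotype.
2. **Alternative:** C_max and AUC24 from a model run without phenotype as a covariate.

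Phenotype-informed parameters can be kept for description.

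**Cost.** No new blood sample is needed. Option 1 needs the time of the last dose recorded at the draw. Option 2 needs one further model run. Its downside is more than lost precision: it keeps the nominal error rate but shrinks a true difference toward 1, to about 1.38 to 1.23 for a true ratio of 1.5 under the assumptions above. Option 1 leaves the ratio unattenuated.

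Option 1 has somewhat lower power than the phenotype-informed test appears to have. With a standard error of √(w² + s²) × 0.218 and a true ratio of 1.5, its power is 98%, 96% and 90% for s = 0.2, 0.3 and 0.4. The phenotype-informed test with the same assumed ratio shows 99.9% or more, but part of that is the assumption itself.
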